### Safety assessments

3.6

Although focusing on prognosis and the QoL of TNBC patients with CHM, the safety of taking CHM is also the focus of attention. Blood routine test, urine routine test, stool routine test, liver and kidney function test were registered at baseline, and each follow-up visit to evaluate whether there is any functional damage after taking CHM. Morevover, tumor makers (CEA, CA125, CA153) were checked in to estimate whether CHM promotes tumor progression. In addition, investigators will ask participants at the time of each follow-up if they have any adverse effects (AEs) include physical discomfort or impairment throughout the course study. If there were any AEs, the investigator would provide appropriate treatment to the patient immediately and record it in the case report form (CRF^∗∗^) in time. At the same time, the severity of the AE and the relationship with CHM should be evaluated. If the AE is related to CHM or had an impact on the patient, the CHM should be stopped immediately and that patient should be closely observed. Meanwhile, details should be reported to the supervisor and recorded in the patient's file.

### Observation time

3.7

Primary endpoint: Local recurrence or distant metastasis.

Study endpoint: Local recurrence or distant metastasis, death, or the end of the study.

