### Primary

2.1

The primary objective of this study is to explore the association of CHM and recurrence and metastasis rate.

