### Study design

3.1

This study is a multicenter, prospective cohort study. The study has started in March 2016 and is currently ongoing. Two hundred and twenty TNBC patients aged between 18 to 75 years with II-III stage after surgery are enrolled from 9 hospitals. All participants need to complete the standard chemotherapy and (or) radiotherapy specified by the National Comprehensive Cancer Network (NCCN) guidelines according to their disease states. At the time of the participants entered the study, the duration of the last chemotherapy and (or) radiotherapy was not more than half a year. The whole study consists of 2 stages, stage I comprises a cross-sectional study-baseline and stage II is a cohort follow-up study across a 3-year period. Participants will be followed up every 3 to 6 months till recurrence or metastasis for 3 years. The feasibility and preciseness of the whole process were supervised by 1 to 2 supervisors.

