#### Primary outcomes

3.4.1

The primary outcome of this study is 3-year disease-free survival and 3-year disease-free survival rate.

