### Sample size calculation

3.5

The primary objective of the research is 3-year DFS rate and we use it as the basis for the calculation of sample size. Referring to the relevant large-scale cohort study,^[18]^ the 3-year DFS rate of TNBC patients after surgery is about 77%, we assume it to be increased to 86%^[19]^ with the treatment of CHM. The sample size calculation formula for cohort study is n = 2p(1-p)(uα + uβ)/(p1-p2),^[2]^ p = (p1 + p2)/2, α assign to 0.05 and β assign to 0.2, the power is 80%, we need 92 participants of each cohort. The drop-out rate is considered as 20%, then the sample size of each cohort is 110 and the total sample size is 220.

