### Statistical analysis

3.8

All statistical analysis will be performed using Statistical Packages of Social Sciences software (SPSS) 19.0. Statistical significance will be defined as the *P* < 0.05. Based on the data distribution, the measurement data will be analyzed by ANOVA or *U* Mann-Whitney test, counting data using *χ*^*2*^test or *U* Mann-Whitney test. The survival data will be analyzed by Kaplan-Meier method in 1, 2, 3-year DFS rate and the recurrence and metastasis rate, then draw the survival curve. The comparison of survival curves between the two cohorts is based on Log-rank method. Repeated ANOVA will be used to evaluate the repeated measures such as the QoL, physical condition, and symptoms related to breast cancer. Evaluation of therapeutic efficiency will be analyzed by the data of full analysis set (FAS) and per protocol set (PPS), safety evaluation will use the data of safety analysis set (SS) for statistical analysis.

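### The primary endpoint is inconsistent on whether a death without recurrence counts as an event

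*Protocol article*

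**What the plan says.** All references are to the protocol article.

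- **Section 3.4.1 (Primary outcomes):** "The primary outcome of this study is 3-year disease-free survival and 3-year disease-free survival rate".
- **Section 3.5 (Sample size calculation):** "The primary objective of the research is 3-year DFS rate and we use it as the basis for the calculation of sample size". The assumed rates are 77% without Chinese herbal medicine (CHM) and 86% with it.
- **Section 3.7 (Observation time), first line:** "Primary endpoint: Local recurrence or distant metastasis".
- **Section 3.7, second line:** "Study endpoint: Local recurrence or distant metastasis, death, or the end of the study".
- **Section 2.1 (Primary objective):** the aim is to "explore the association of CHM and recurrence and metastasis rate".
- **Section 3.1 (Study design):** "Participants will be followed up every 3 to 6 months till recurrence or metastasis for 3 years".
- **Section 3.8 (Statistical analysis):** survival data go to the "Kaplan-Meier method in 1, 2, 3-year DFS rate and the recurrence and metastasis rate", and the cohorts are compared by log-rank test.

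The article nowhere lists the events that make up DFS and nowhere says how a death without recurrence is handled.

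**The concern.** Sections 3.4.1 and 3.5 name a composite that, by the ordinary meaning of DFS, a death would end. Section 3.7 gives a primary endpoint without death, then a second list that adds death beside the administrative end of the study. With the two lists next to each other, a reader can fairly conclude that death stops observation without being a primary event. In a Kaplan-Meier analysis, a patient whose observation stops without the event is censored.

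Two analysts, one working from section 3.4.1 and the other from section 3.7, would count different events and could report different primary results from the same data. The cohorts are not randomised, so equal numbers of deaths without recurrence cannot be presumed. If the conflict stays open until the data are seen, the event definition could also be chosen after the result is known.

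**Working it through.** **1. The passages side by side**

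| Section | Primary quantity | Does a death without recurrence count? |
|---|---|---|
| 3.4.1 | 3-year DFS and its rate | Yes on the usual meaning of DFS; not spelled out |
| 3.5 | 3-year DFS rate | As above |
| 3.7, first line | Recurrence or metastasis | No |
| 3.7, second line | What ends the study for a patient | Death listed, beside end of study |
| 2.1 | Recurrence and metastasis rate | Not mentioned; an objective, not an endpoint definition |
| 3.8 | DFS rate and, named separately, recurrence and metastasis rate | Not stated |

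The conflict lies between 3.4.1 and 3.5 on one side and the first line of 3.7 on the other. Section 2.1 adds little, because an objective in clinical terms can be measured by DFS.

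**2. Effect if section 3.7 governs**

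Inputs: 3-year DFS of 77% and 86% (section 3.5), taken to include deaths. Let q be the share of DFS events that are deaths without recurrence. The article gives no value for q, so the range is an assumption.

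Formula: with proportional cause-specific hazards and deaths censored, the Kaplan-Meier estimate tends to S^(1−q), where S is true DFS. Example for q = 10%: 0.77^0.90 = 0.7904 and 0.86^0.90 = 0.8731.

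| q | No CHM | CHM | Overstatement (no CHM / CHM), points | Difference, points |
|---|---|---|---|---|
| 0 | 77.00% | 86.00% | 0 / 0 | 9.00 |
| 2% | 77.40% | 86.26% | 0.40 / 0.26 | 8.86 |
| 5% | 78.01% | 86.65% | 1.01 / 0.65 | 8.64 |
| 10% | 79.04% | 87.31% | 2.04 / 1.31 | 8.27 |
| 20% | 81.13% | 88.63% | 4.13 / 2.63 | 7.50 |

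The row q = 0 returns the plan's own rates.

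**3. Sensitivity to the equal-share assumption**

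Suppose instead that the same percentage d of all patients in each cohort dies without recurrence, so q = d/0.23 without CHM and q = d/0.14 with CHM.

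- d = 1%: 77.88% and 86.93%, difference 9.05 points.
- d = 3%: 79.67% and 88.82%, difference 9.15 points.

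The overstatement of each rate remains, but the difference hardly moves. The narrowing in step 2 depends on q being equal in the two cohorts.

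**4. Kaplan-Meier for the recurrence and metastasis rate**

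With S = 77% and d = 1% or 3%, one minus Kaplan-Meier gives 100 − 77.88 = 22.1% or 100 − 79.67 = 20.3%. The cumulative incidence is 23 − 1 = 22.0% or 23 − 3 = 20.0%. The gap is about 0.1 to 0.3 points.

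**5. The plan's sample size**

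The stated 92 per cohort does not reproduce with the standard two-proportion formula (292 two-sided, 230 one-sided). That is a separate matter, and nothing above depends on it.

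**The case against.** The strongest objection is to a stronger reading that a reader might infer: that the plan censors deaths and therefore overstates DFS. The article does not establish this. It states no censoring rule. Section 3.8 names DFS and the recurrence and metastasis rate as separate quantities, which suggests that DFS is not simply the complement of recurrence. Section 3.7 is headed as a section on observation time, so its second line can be read as the DFS events plus administrative end. DFS could still count deaths. This objection stands, and the overstatement is therefore only conditional.

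A second objection is that a condensed article may leave the DFS event list to a fuller protocol or analysis plan. That is fair for the missing list. It does not excuse two incompatible statements of the primary event in the article itself.

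A third objection is that the effect may be negligible in stage II-III patients followed for 3 years after surgery. That also stands, since the article gives no rate of death without recurrence. A reader might further infer that a few such deaths would decide significance. At the design rates, about 0.14 × 110 = 15 and 0.23 × 110 = 25 events are expected per cohort. An uncorrected chi-square test gives P = 0.080 for 15 against 25 and P = 0.040 for 15 against 27. That shift needs both extra deaths to fall in one cohort, for which the article gives no basis, and the counts ignore the planned 20% drop-out. It is an illustration only.

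Finally, the competing-risk issue in section 3.8 is real in principle but worth only about 0.1 to 0.3 points under the assumptions in step 4. It does not carry the point.

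**Conclusion.** The contradiction stands: sections 3.4.1 and 3.5 make DFS primary, while section 3.7 gives a primary endpoint that leaves out death. It concerns the primary event and has to be reconciled.

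The numerical consequence is conditional on section 3.7 governing the primary analysis. In that case the direction is certain whenever a death without recurrence occurs: the estimate lies above true DFS. The size is unknown. It is zero with no such deaths, and about 0.3 to 4.1 points if they make up 2% to 20% of DFS events. The target difference then falls from 9 to between 8.9 and 7.5 points if that share is equal in both cohorts. These figures assume proportional cause-specific hazards and that the 77% and 86% already include deaths.

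**What to change.** Before analysis, carry one primary event definition through sections 3.4.1, 3.5 and 3.7, and align the wording of 2.1 with it. A DFS event is the first of local recurrence, distant metastasis or death from any cause. Censor only at the last disease-free assessment or the end of the study. In section 3.7, label the second list as what ends observation, so that it cannot be taken for a rival endpoint.

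Report recurrence and metastasis as a separate secondary outcome. Estimating it by cumulative incidence (Aalen-Johansen), with death without recurrence as the competing event, is an optional refinement with little numerical effect.

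The cost is wording in four sections, plus one extra estimate if the refinement is taken up. No new patients or visits are needed, because death already ends observation under section 3.7.

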### Statistical analysis

3.8

All statistical analysis will be performed using Statistical Packages of Social Sciences software (SPSS) 19.0. Statistical significance will be defined as the *P* < 0.05. Based on the data distribution, the measurement data will be analyzed by ANOVA or *U* Mann-Whitney test, counting data using *χ*^*2*^test or *U* Mann-Whitney test. The survival data will be analyzed by Kaplan-Meier method in 1, 2, 3-year DFS rate and the recurrence and metastasis rate, then draw the survival curve. The comparison of survival curves between the two cohorts is based on Log-rank method. Repeated ANOVA will be used to evaluate the repeated measures such as the QoL, physical condition, and symptoms related to breast cancer. Evaluation of therapeutic efficiency will be analyzed by the data of full analysis set (FAS) and per protocol set (PPS), safety evaluation will use the data of safety analysis set (SS) for statistical analysis.

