### Study settings and participants

3.2

The study is being performed in 9 hospitals in Beijing include Beijing traditional Chinese Medicine Hospital affiliate to Capital Medical University, China-Japan Friendship Hospital, People's Hospital of Peking University, Chinese PLA General Hospital, Cancer Hospital of Chinese Academy of Medical Science, Guang’Anmen Hospital of the China Academy of Traditional Chinese Medicine, Beijing Tiantan Hospital affiliate to Capital Medical University, Beijing Luhe Hospital affiliate to Capital Medical University, and Beijing Shijitan Hospital affiliate to Capital Medical University. All TNBC patients who came to the above hospitals should be screened. For those eligible patients, researchers will give her and her guardian the detailed description of this study. After obtained the informed consent of the patient and her family, she was enrolled in the study. Participants taking CHM in 1 of the above 9 hospitals were referred to as cohort 1 and patients received chemotherapy or radiotherapy without CHM belong to cohort 2. Doctors of traditional Chinese medicine in the above hospitals prescribe CHM for patients according to their clinical symptoms, tongue and pulse, doctors at the above nine hospitals will also provide life guidance for these TNBC patients. The study schema and estimated recruitment numbers are presented in Figure 1. Inclusion and Exclusion criteria are presented in Table 1. Two investigators will be responsible for the follow-up of each participant at baseline and every 3 to 6months, data collection schedule is presented in Table 2.

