## Discussion

4

CHM has been used for thousands of years in China. In recent years, it has been gradually accepted by Western countries.^[20]^ Thus far, literatures^[21,22]^ reported that CHM is widely used to reduce the side effects of chemotherapy and increase survival of patients, antitumor immune response and the general state of the patients. Also, research^[23]^ reported that CHM combined with chemotherapy can improve survival rate and the quality of life. To evaluate the relationship between CHM and tumor recurrence and metastasis, we choose a simple disease TNBC as the research type. So far it has no other therapeutic regimen besides chemotherapy and radiotherapy after surgery and we can eliminate interference from other treatment factors.

There are several strengths in our study. First, this is the first multicenter prospective observational cohort study on CHM in TNBC patients. There are 9 hospitals participating in this study. It can provide the evidence both relatively objective and consistent with the clinical practice of CHM intervention for TNBC. Second, we choose the observational study design as it is more humanistic than randomized controlled trial (RCT). Although RCT is recognized as the highest level of evidence in the field of evidence based medicine (EBM), it faces a series of ethical challenges for patients with cancer, especially for the research related to survival time. However, the observational cohort study greatly values individual willingness for the choices of treatment and maximize the applicability of CHM in clinical practice.^[24]^ Third, doctors write out a prescription based on the patient's TCM syndrome differentiation^[25]^ instead of roughly dividing into a few types of syndrome. This improves not only the accuracy of syndrome differentiation, but also the pertinence of CHM. Lastly, the study will produce a scroll queue of TNBC that is not only used for this study, but the relevant information from the rolling queue will continue to be followed up and recorded to provide effective and detailed information for the subsequent researches.

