Some limitations of this study are as follows. In the field EBM, the cohort study is an observational study and the evidence level is lower than RCT.^[26]^ But after weighing the research program and the patients’ interests, we choose to maximize the latter one to use a cohort study. In addition, there may be an imbalance baseline condition between the two cohorts. To resolve the problem, we will analyze the data at different levels according to different stages of disease, age, and other possible related factors. Since it is a cohort study, queue migration is inevitable. Strengthening the management of follow-up of participants is one of the effective ways to avoid the problem. Patients will be followed up every 3 to 6 months, their medication and physical conditions will be recorded in detail in the CRF. Finally, there are only 220 TNBC patients will be recruit and the sample size looks small for a prospective cohort study. Yet it is limited by research period and funding. Nevertheless, the observation for the TNBC participants take part in this study won’t be stopped three years later. We will continue to follow up these participants to get a long-term information and then to analyze and evaluate the effect of TCM on TNBC more accurately.

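### The primary DFS curves of self-selected cohorts are compared by an unadjusted log-rank test, and the promised analysis by levels is not tied to that comparison or pooled into one adjusted estimate

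*Protocol article*

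**What the plan says.** Section 3.4.1 of the protocol article sets the endpoint: "The primary outcome of this study is 3-year disease-free survival and 3-year disease-free survival rate". Section 3.8 sets the test: "The comparison of survival curves between the two cohorts is based on Log-rank method". The other between-group tests listed there for continuous and count data (ANOVA, Mann-Whitney, chi-square) are unadjusted too. If the 3-year rate were compared by chi-square rather than read from the curves, that comparison would also be crude.

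Section 3.2 defines exposure by use: "Participants taking CHM in 1 of the above 9 hospitals were referred to as cohort 1". Patients treated without CHM form cohort 2. The Discussion presents patient choice as a strength of the design: "the observational cohort study greatly values individual willingness for the choices of treatment". Its limitations paragraph concedes that the cohorts may differ at baseline and offers this as the solution: "we will analyze the data at different levels according to different stages of disease, age, and other possible related factors".

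**The concern.** The primary objective is the association of CHM with recurrence and metastasis. Patients who seek CHM may differ from those who do not in stage, age, fitness or treatment received. A log-rank test without strata or covariates attributes any resulting difference in prognosis to CHM.

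The article sees the problem and names a remedy, but leaves three things unsettled:

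- The factor list is open and has no cut-points.
- Nothing says whether results by level are pooled.
- Nothing says whether they replace, qualify or merely accompany the log-rank test in section 3.8.

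Followed as written, the study could report a crude p-value as its main result, next to a set of small subgroup results chosen after the data are seen.

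**Working it through.** **Inputs from section 3.5:** 3-year DFS 77% without CHM and 86% with CHM; 92 per cohort, 110 after allowing for dropout; dropout 20%; α 0.05.

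**The plan's own figures.** 92 × 1.2 = 110.4, which gives the stated 110. The 92 itself does not reproduce: the usual squared formula, 2 × 0.815 × 0.185 × (1.96 + 0.842)² / 0.09², gives about 292 per cohort two-sided. That is a separate matter; only the stated 110 and the two rates are used below. The article gives no event count.

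**Expected events.** With no loss: 110 × (0.23 + 0.14) = 40.7. With 20% lost entirely (88 per cohort): 88 × 0.37 = 32.6.

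**Precision by level.** The implied hazard ratio is ln 0.86 / ln 0.77 = 0.577, so |ln HR| = 0.550. Schoenfeld power, two-sided, is Φ(√(d/4) × 0.550 − 1.96). The 95% limits are roughly the HR divided and multiplied by exp(1.96 × 2/√d). Levels are assumed equal in size, with no loss.

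| Levels analysed separately | Events each | Power each | 95% limits: HR ÷/× |
|---|---|---|---|
| 1 (all patients) | 40.7 | 42% | 1.8 |
| 2 | 20.4 | 24% | 2.4 |
| 4 (e.g. stage × age) | 10.2 | 14% | 3.4 |
| 8 | 5.1 | 9% | – |

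With 32.6 events, the whole study has 35% power, and four levels would hold about 8 events each.

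**Bias of the crude test (all imbalances assumed).** Suppose CHM has no effect, cohort 2 has 3-year DFS of 77%, and half of cohort 2 is stage III. Let x be 3-year DFS in stage II. With a stage III HR of 2, 0.5x + 0.5x² = 0.77 gives x = 0.838 and x² = 0.702. If only 30% of cohort 1 is stage III, its DFS is 0.7 × 0.838 + 0.3 × 0.702 = 0.797, a spurious gain of 2.7 points. The other rows follow in the same way. The last two columns are simulated (110 per cohort, 20% loss, 4,000 runs); the nominal rate is 2.5%.

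| Stage III, cohort 2 vs 1 | Stage III HR | Spurious gain | Falsely favours CHM, crude | Same, pooled stage-stratified log-rank |
|---|---|---|---|---|
| 50% vs 30% | 2 | 2.7 points | 6.8% | 2.7% |
| 50% vs 30% | 3 | 4.1 points | 10.1% | 2.5% |
| 50% vs 20% | 2 | 4.1 points | 10.2% | 2.3% |
| 50% vs 20% | 3 | 6.2 points | 20.6% | 2.2% |

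A second simulation fixed pooled DFS at 81.5% (5,000 runs). For 50% vs 30% at HR 2.5 it gave 8.4%, and for 60% vs 30% at HR 3 it gave 17.2%. For a small imbalance, 50% vs 40% at HR 2, it gave only 3.8%, with total two-sided error of 5.1%.

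**A factor left out of the strata.** With an assumed HR of 2.5 and prevalence of 60% vs 30%, total two-sided error was 13.9% crude and 13.8% after stratifying by stage. Pooling over stage does nothing for it.

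**The case against.** The best defence is that analysis by levels can be read as a stratified analysis with a pooled result. Stage is the first factor the Discussion names, and a pooled stage-stratified log-rank test brings the error back to nominal in every stage scenario above. That stands: it would be wrong to say that stratification cannot help. But the article names no pooled test, closes no factor list, and leaves the test in section 3.8 crude.

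The article also condenses a fuller protocol, an analysis plan may exist, the objective is exploratory, and the risk of imbalance is disclosed. This is fair on covariate detail. It does not cover a named crude test and a named remedy that are not connected to each other.

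The imbalances are assumed. No section gives the stage mix by cohort or a stage hazard ratio. This also stands.

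Two stronger readings are tempting but unsupported:

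- A reader might set the Discussion's statement "we can eliminate interference from other treatment factors" against section 3.1: "All participants need to complete the standard chemotherapy and (or) radiotherapy specified by the National Comprehensive Cancer Network (NCCN) guidelines according to their disease states". In context, the Discussion means treatments beyond chemotherapy and radiotherapy, so variation in those two does not contradict it, and the sentence need not be removed.
- A reader might infer from the hospitals' names that some do not offer CHM. Section 3.2 says that TCM doctors in the listed hospitals prescribe it, so a difference in availability is not shown.

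**Conclusion.** The point holds in a limited form. The only test stated for the primary survival curves is unadjusted, in cohorts formed by choice, and the stated remedy neither enters that comparison nor yields one adjusted estimate. With about 33 to 41 events, results by separate level would be too imprecise to stand in for one.

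Under assumed stage imbalances of 20 to 30 points favouring CHM and a stage III HR of 2 to 3, the crude test would falsely favour CHM in roughly 6% to 20% of studies instead of 2.5%. The spurious gain of 2.7 to 6.2 points is part, not all, of the 9-point difference sought. Smaller imbalances matter less, and reversed ones would hide a benefit. The documents do not show that the cohorts are in fact imbalanced, or in which direction. A reader might conclude that any CHM difference will be an artefact; that does not follow.

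**What to change.** Make the primary between-cohort analysis one prespecified adjusted analysis that uses all events. The simplest version is a Cox model for CHM stratified by stage (II or III) and adjusted for age and one or two other baseline prognostic factors, with the list closed before outcomes are compared. By the assumed rule of ten events per parameter, 40.7 events support about four parameters including CHM, and 32.6 about three. A propensity-score-weighted Cox model with robust standard errors is a reasonable alternative, or a sensitivity analysis. Choose only factors recorded at baseline; the data collection table is not visible here, so this needs checking.

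Keep the Kaplan-Meier curves and the crude log-rank test as descriptive. State in section 3.8 how the by-level results in the Discussion relate to the primary result, and label them exploratory. Word conclusions as an adjusted association with possible residual confounding.

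The cost is revised wording and a little programming; no extra patients are needed. Some precision is lost, more so if hospital is included and the cohorts overlap little within hospitals. No adjustment removes confounding by factors that were not recorded.

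### The tests named in section 3.8 carry no hospital term in a non-randomised nine-hospital cohort, so hospital differences could confound the CHM comparison in either direction

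*Protocol article*

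**What the plan says.** All references are to the Protocol article.

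- **Study design (3.1):** "Two hundred and twenty TNBC patients aged between 18 to 75 years with II-III stage after surgery are enrolled from 9 hospitals".
- **Study settings and participants (3.2), exposure:** "Participants taking CHM in 1 of the above 9 hospitals were referred to as cohort 1". I read this as CHM taken at any one of the nine. On prescribing: "Doctors of traditional Chinese medicine in the above hospitals prescribe CHM for patients according to their clinical symptoms, tongue and pulse". Patients are not randomised.
- **Study settings and participants (3.2), sites:** two of the listed hospitals are TCM institutions by name, one of them "Guang’Anmen Hospital of the China Academy of Traditional Chinese Medicine". The others are general or cancer hospitals.
- **Statistical analysis (3.8):** for disease-free survival (DFS), "The comparison of survival curves between the two cohorts is based on Log-rank method". For quality of life (QoL) and symptoms, "Repeated ANOVA will be used to evaluate the repeated measures such as the QoL, physical condition, and symptoms related to breast cancer". ANOVA, Mann-Whitney and chi-square tests cover the rest. No stratum, covariate or hospital term is attached to any of them.
- **Discussion (4):** the multicentre design is presented as a strength ("There are 9 hospitals participating in this study"). For baseline imbalance the plan is: "we will analyze the data at different levels according to different stages of disease, age, and other possible related factors". Hospital is not named in that list, but the list is open.

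**The concern.** In a randomised trial stratified by site, leaving site out of the test usually does little harm. Here exposure depends on patient choice and on TCM prescribing, so nothing in the design balances the cohorts within hospitals. With two TCM hospitals among general and cancer hospitals, the CHM share could well vary from site to site.

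Outcomes could also vary by site for reasons unrelated to CHM. Visits may fall anywhere from 3 to 6 months apart, which affects when a recurrence is dated. Several imaging methods are listed as alternatives. Doctors at each hospital also give lifestyle guidance, which could move QoL scores. Adjusting for stage and age removes none of this.

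If both links exist, a pooled two-cohort test attributes part of the hospital difference to CHM. At stake are the primary DFS comparison and each QoL and symptom test judged at P < 0.05.

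**Working it through.** The article gives no CHM share by hospital, no hospital-level DFS and no within-hospital correlation. There is therefore no planned figure to reproduce on this point, and every size below rests on stated assumptions.

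**Inputs from the article.** 220 patients in 9 hospitals, 220/9 = 24.4 per hospital on average; 3-year DFS 77% without and 86% with CHM, mean (77 + 86)/2 = 81.5%; 20% drop-out; 3 years of follow-up; significance at 0.05.

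**1. Confounding with no CHM effect.** Assume three hospitals with 90% CHM use and 83% DFS, and six with 30% CHM use and 74% DFS, all of equal size.

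- CHM cohort: (3×0.9×0.83 + 6×0.3×0.74)/(2.7 + 1.8) = 3.573/4.5 = 79.4%
- Other cohort: (3×0.1×0.83 + 6×0.7×0.74)/(0.3 + 4.2) = 3.357/4.5 = 74.6%
- Spurious difference: 4.8 points, against the 9 points the study is planned to find.

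With CHM shares of 70% and 40% the result is 78.2% − 75.8% = 2.4 points. If the two DFS values are exchanged between the hospital groups, the sign reverses: at 90% and 30% it is 77.6% − 82.4% = −4.8 points.

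**2. False-positive rate of the pooled log-rank test.** Simulated with no CHM effect, a normal hospital effect on the log hazard and a nominal level of 5%. Set A: nine hospitals of 24, DFS 81.5%, 4,000 runs. Set B: 220 patients in nine equal hospitals, DFS 77%, 3,000 runs. Both have about 20% drop-out. At a true 5%, simulation error is about ±1.96×√(0.05×0.95/3000) = ±0.8 points in set B, and slightly less in set A.

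| CHM share by hospital (set) | SD 0.3 | SD 0.5 |
|---|---|---|
| Equal in all (B) | 5.0% | 4.9% |
| 3 at 70%, 6 at 40% (B) | 5.4% | 6.2% |
| 80:20 or 20:80 (A) | 6.7% | 9.0% |
| 3 at 90%, 6 at 30% (B) | 6.1% | 9.5% |
| 90:10 or 10:90 (A) | 7.2% | 12.1% |
| Nearly all-or-none (A) | 7.8% | 15.7% |
| 4 at 95%, 5 at 5% (B) | 9.7% | 16.1% |

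A repeat simulation gave 6-8% at 80:20 and 7-13% at 90:10. Stratifying by hospital gave 4.2% to 6.1% throughout set B, and about 5-6% in set A at 80:20 and 90:10.

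**3. QoL scores.** With a within-hospital correlation of 0.05 / 0.10, the pooled test rejects in 8.6% / 13.9% of null studies at 80:20 and 12.3% / 20.5% at 90:10. A hospital fixed effect brings these back to about 5-6%. As an outer bound, if exposure were set wholly by hospital, the design effect is 1 + (24.4 − 1)×ICC. That is 1.23, 1.47 and 2.17 at ICC 0.01, 0.02 and 0.05, an effective total of 178, 150 and 101 patients.

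**4. Price of stratifying.** Information kept at an 80:20 split is 4×0.8×0.2 = 64%, so 36% is lost (about 35% by simulation). With equal shares, the loss from small strata is about 1/24.4 = 4% at the outset and about 5% once risk sets shrink.

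**The case against.** A reader might infer more than the article supports: that CHM use follows hospital type, that every analysis ignores hospital, and that the P values are therefore too small. Four objections count against that reading.

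- **The link is inferred from hospital names.** Section 3.2 allows CHM at all nine sites, with TCM doctors prescribing there. With equal or mildly unequal shares the pooled log-rank stays near 5%. This stands: the error rate may be wrong, but it has not been shown to be.
- **Shared care is not documented.** Patients enter after surgery and after guideline-based chemotherapy and/or radiotherapy, so the enrolling hospital need not be where they were treated. This weakens the case for large hospital effects. It leaves possible differences in visit timing, imaging and local guidance.
- **The larger figures need large effects.** An SD of 0.5 around 81.5% puts 95% of hospitals between 0.815^2.66 = 58% and 0.815^0.375 = 93% for 3-year DFS, which is very wide. At SD 0.3 the range is 69% to 89% and DFS inflation is modest. This stands.
- **Site handling may sit elsewhere.** The Discussion's list is open, and a statistical analysis plan not shown could add hospital. So it cannot be said that all analyses will pool. The point rests on the test that is named and the factors that are named, not on silence alone.

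A further objection concerns the remedy. At most 220×0.185 = 41 events are expected, about 4-5 per hospital. Two-sided power for 77% against 86% with 110 per cohort is about 40%: 0.09/√(2×0.815×0.185/110) = 1.72, and Φ(1.72 − 1.96) = 0.40. Keeping 64% of the information gives Φ(1.72×0.8 − 1.96) = 0.28. That is a fair reason not to replace the pooled test outright. Grouping sites into TCM and non-TCM strata does not help where those strata almost match the cohorts.

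**Conclusion.** The concern holds in conditional form. Section 3.8 names pooled tests without a hospital term, and hospital is absent from the named adjustment factors, in a design where exposure is self-selected and the sites differ in kind. If CHM use and outcome both vary by hospital, the CHM comparison is confounded, in favour of CHM or against it. Confounding is the main problem; understated variance is secondary.

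Under the assumptions above, the true error rate is about 5% with equal shares, and 6-13% for DFS and 9-20% for QoL scores at 80:20 to 90:10 splits (hospital SD 0.3-0.5 on the log hazard; within-hospital correlation 0.05-0.10). None of these inputs is in the article. The size is therefore a range to guard against, not an estimate for this study.

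**What to change.** In section 3.8, before the cohorts are compared:

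1. Tabulate cohort by hospital.
2. Add hospital as a fixed or random effect to the QoL and symptom models. A fixed effect compares patients within hospitals; a random effect alone does not fully remove confounding.
3. Pre-specify a log-rank test stratified by hospital, or a Cox model stratified by hospital, reported beside the pooled test.
4. Require any CHM conclusion to be consistent with the stratified result, and write down in advance what counts as consistent.
5. Name hospital among the imbalance factors in the Discussion.

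No new data are needed, since each patient's hospital is known. The cost is precision: about 5% of information with equal shares and about 35% at 80:20, and hospitals contributing only one cohort add nothing to a stratified test. Where hospital and cohort nearly coincide, neither stratification nor a random effect can separate them. The report should then state this as a limitation.
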